**Fig. 2 Fig2:**
[figure not shown]
Graphical Representation Options for Sedentary Time. Legend. Graphic 1: Meter; Graphic 2: Pie chart; Graphic 3: Line graph

#### Pilot testing

A brief pilot test was conducted among nine individuals to test the final smartphone app for functionality, to determine the feasibility of the recruitment strategies and protocol, and to gather final feedback to refine prior to the main trial. These participants, all of whom met the eligibility criteria for the upcoming main trial, were recruited using the adapted recruitment approaches (including social media, email/word-of-mouth, and flyers). The social media stand-alone study pages on Facebook, Twitter, and Instagram were launched simultaneously with an email campaign to the CAB and community contacts to request that they share and re-post information about the study. Throughout the pilot test, we posted social media messages five to seven times per week. These messages described study eligibility and activities, highlighting aspects of the study that FG participants had identified as appealing, including involving local coaches, technology, and financial incentives. Messaging also featured local community member involvement in the adaptation and project, introduced study personnel, provided information updates, and included a link to a study webpage where participants could volunteer by completing an online screener. We aimed to recruit participants for both the intervention condition (diet, physical activity, sedentary behavior) and the control condition (stress, sleep); thus, the messages were broad and referenced healthy lifestyles. During the pilot study, we “boosted” one message on Facebook, paying the online platform to increase the visibility of the message. All other messages relied on friends/followers to increase their visibility by interacting with the message.

Most interaction with social media occurred on the Facebook page, through which people interacted with our posts a total of 3,206 times. These interactions included reacting to a post, clicking on the survey link, and commenting. Neither Twitter nor Instagram generated many followers or interactions. Lack of engagement with these platforms is unsurprising, given high use of Facebook and low use of other social media platforms in rural areas [36].

A total of 218 people completed the eligibility survey during the pilot period and, of those, 165 (75.7%) indicated how they had learned about the study. Most (63.6%, *n* = 105) learned about the study from Facebook, although word-of-mouth (27.3%, *n* = 45) also contributed to recruitment. We launched our social media pages (Facebook, Instagram, Twitter) with messages that promoted the study and the study’s website. The social media messages included details of the study and directed those who were interested and potentially eligible to our website and screening survey.

##### Eligibility and screening

Consistent with the upcoming main trial, to be eligible for the pilot test, candidates had to meet the following criteria: being adults age 18 or older from any of the 54 counties in Appalachian Kentucky; willing to use their smartphone to record and modify diet, physical activity and sedentary behavior, and to wear a Fitbit for 12 weeks and intermittently thereafter for up to one year. Those with unstable medical conditions required physician approval to participate. To ensure the relevance of the treatment/behavioral change, we limited inclusion to those individuals who reported all of four problematic diet and physical activity behaviors: consuming < 4.5 cups of fruits/vegetables daily; engaging in < 150 min of moderate intensity physical activity weekly; and spending > 8 h daily of sedentary time (including sitting or lying down but not sleeping). We excluded individuals with cognitive impairment, active suicidal ideation, substance use disorder other than nicotine dependence, those at risk for adverse cardiovascular events with moderate intensity activity, and those with anorexia, bulimia, or other eating disorders or adhering to an incompatible dietary regimen. We also excluded those hospitalized for a psychiatric disorder within the past 5 years.

Three screening stages were used to assess eligibility. First, interested individuals used an online screener accessed through the study website. Those initially eligible were contacted by staff members via phone, text messaging, and/or email to schedule a telephone call to undertake the verbal informed consent process for screening and further determine eligibility. Third, individuals were emailed a link to the study’s baseline online questionnaire to be completed at home within one to two weeks. Once the baseline questionnaire was complete, those who remained eligible were permitted to select either an in-person or a remote baseline assessment.

##### Assessment and participant training

For the pilot test of the intervention, outcome data were collected in person at two time points: baseline and posttest. During baseline assessments, biometric data (blood pressure, lipids, A1C, waist circumference, BMI) were collected and additional surveys were completed. Fitbits, used in place of research-grade accelerometers (as advised by wireframe participants and the CAB due to Fitbit’s extra features and convenience), were distributed, and staff members trained participants on the health app, with specific focus on food logging and portion sizes. Training consisted of wearing a Fitbit and using the smartphone health app to record diet, physical activity, sleep, and stress data. The health coach and/or technician made a check-in/trouble-shooting call on the day after the participant began data entry. To ensure that participants were confident and competent in the use of the app, these data were viewed as practice tests rather than baseline data. The identical process was repeated one week later to collect the baseline data. All data were transmitted to the secure data platform via REDCap. Eligible participants were assigned to one of two intervention conditions: diet and activity or stress and sleep. A full description of the adapted intervention is described below.

##### Pilot results

Of the nine participants, six were assigned to the diet and activity condition and three were assigned to the stress and sleep condition. Eight of the participants completed all assigned coaching calls and one completed three of the five calls. Pilot participants noted several technical bugs in the smartphone application that were later addressed. Participants also requested improvements to the app such as the ability to see prior tracking episodes, push notifications to remind to track, and additional instruction and practice in logging food. Travel to the main site for the trial was noted as a concern for several participants which we have now addressed by providing a remote option. During exit interviews, pilot participants noted benefits of the interventions including enhancing insight regarding health behaviors, supporting accountability from the health coaches, and recognizing that healthy living is not striving for perfection but about attempting to make sustainable and long term healthy lifestyle decisions. Participants may not be involved in another diet, exercise, or weight control program. All other concomitant care and interventions are permitted during the trial.

### Description of the adapted MBC2 intervention

#### Overview

After minor refinements to the app, we began implementing the MBC2 type 1 hybrid effectiveness-implementation trial. The main trial eligibility criteria, assessment content and schedule, and overall protocol will be identical to the pilot test protocol with several exceptions. In the main trial, participants will be randomized to one of two conditions; it lasts longer, data are collected at baseline plus three points in time, the intervention uses the revised app, and has been expanded to include iPhone as well as Android smartphone users. Figure 3 summarizes the protocol sequence, which includes the two-tiered assessment of eligibility, baseline assessment, randomization, 12 weeks of telephone-delivered coaching, and three outcome assessment periods in addition to a baseline (weeks 13, 26, and 39). In weeks 13–24, participants will enter the early maintenance phase with an in-person assessment and bi-weekly health coaching calls. During weeks 25–39, participants will enter the later maintenance phase by completing another in-person assessment and monthly health coaching calls. In week 40 (month 9), participants will complete the final assessment. Participants in both conditions (*N* = 350) will have the same number and duration of in-person assessments and telephone contacts over the 40 weeks. Only the coaching content and the visual displays will differ between the two conditions, reflecting the distinct behavioral foci.

**Fig. 3 Fig3:**
[figure not shown]
MBC2 for Rural Appalachians Flow Chart

#### Ethics and dissemination

All procedures were approved by the University of Kentucky’s Office of Research Integrity’s Medical Institutional Review Board (IRB). Protocol modifications have been and will be submitted to the IRB. In the future, we would submit any major modifications to scientific conduct to the study sponsor, the National Institutes of Health. Written informed consent was obtained from all participants prior to study procedures. Informed consent was obtained by the project manager and staff, all of whom will obtain needed certifications. All data are stored in a password-protected, firewalled system. While risks related to the intervention and attention control arms are anticipated to be minor, we maintain a data safety and monitoring plan and board (DSMB). All adverse events that do occur will be reported to PI who informs the IRB and DSMB. Participants may withdraw at their discretion. A publication plan and presentation plan has been developed and, as a community trial, results will be transmitted to relevant community partners during informational forums.

#### Adapted MBC2 intervention content

The program consists of four interconnected components: (1) app, (2) health coaching, including weekly lessons for participants, (3) Fitbit, and (4) behavioral incentives. These components encompass behavioral and implementation principles (effectiveness, scalability, and synergy), and they align with Goal Systems Theory. In addition to drawing upon Goal Systems Theory, the MBC2 intervention framework is enhanced by sociocultural and environmental considerations and blends well with the Consolidated Framework for Implementation Research [12, 29, 37].

##### App

This app incorporates a decision support system and display that helps participants monitor fruit & vegetable intake, moderate-vigorous physical activity (MVPA), and sedentary time relative to their daily target. The app also transmits this information to a web-based dashboard that is accessible to health coaches, enabling them to tailor telephone counseling to each participant’s progress and goals. During in-person training, participants are given materials to help them learn to estimate portion size. They also receive reminders that entries are time- and date-stamped to encourage prompt entry. The app automatically uploads data wirelessly, which enables detection of entry error or non-adherence to protocols. App features designed to support participants’ adherence to personal goals include (a) visual displays that provide feedback about intake and expenditure relative to targets throughout the day to guide self-regulation; (b) ability to access smartphone diet and physical activity databases to support decision-making about diet and physical activity choices; and, (c) use of stepped goals to facilitate incremental attainment of targets. In addition to app data, survey data about diet, physical activity, and sedentary behavior data will be collected at the assessment periods (baseline and weeks 13, 26, and 39) to assess intervention effectiveness.

##### Health coaching

Health coaching, evidence-based and strongly supported in our developmental research, comprises a central feature of the MBC2 intervention [33, 38]. For the main trial, coaches will (1) meet in person (or remotely, depending on the participant’s preference) with their assigned participant to help with training on the app and Fitbit and to set individualized goals; (2) provide weekly telephone counseling calls that address behavioral skill building and problem solving, tailoring recommendations to the resources of the community, participants’ preferences and stated challenges; (3) deliver online didactic lessons; (4) provide support and maintain accountability for self-monitoring behavior and initiating healthy change; and, (5) sustain support during the early maintenance phase (bi-weekly, weeks 13–24) and later maintenance phase (monthly, weeks 25–40).

Health coaches are recruited locally and must be comfortable with technology, knowledgeable about local context, and have excellent interpersonal and communication skills. In addition to our three current coaches, we anticipate recruiting and training three more coaches, allowing for the likely event that several coaches will leave or fail to meet fidelity criteria which will be assessed by anonymized reviewers. All coaches undergo extensive training in human subjects protection, app and Fitbit use, diet and physical activity, and brief, remotely-delivered health promotion techniques, including motivational interviewing (MI). All coaches are trained and certified through didactic sessions, role-play exercises, practice calls, and direct observation over several weeks until core competencies in MI and the research protocol are met. To maximize fidelity, all sessions are guided by scripts and checklists. Coaches avoid contamination across intervention conditions (e.g., coaches in the active MBC2 diet and activity treatment arm encourage physical activity but avoid addressing stress or sleep). Prior to intervening with study participants, all coaches must reach 100% proficiency by demonstrating core coaching skills and treatment fidelity benchmarks during three practice phone calls. Ongoing direct observation, immediate feedback after coaching sessions, and weekly clinical supervision via video conference will be implemented to prevent drift from approach and protocol over time. All subsequent coaching sessions will be audio-recorded, and a random 10% will be assessed quarterly for fidelity using a checklist. Because the primary focus of type 1 hybrid effectiveness-implementation studies is on effectiveness, fidelity will be maximized using these rigorous methods developed and used in prior MBC studies. In this context, intervention fidelity is required to ensure the quality of the delivered treatment (the trial’s independent variable), rather than treated as an implementation outcome.

##### Fitbit

Participants will be given a Fitbit Inspire 2 to wear daily on the non-dominant wrist during the intervention. To provide feedback to participants, the Fitbit data for MVPA, inactive minutes, and sleep will be sent via the application programming to be displayed on the study smartphone application as time spent in each behavior relative to goals.

##### Behavioral incentives

An incentive ($5) will be provided weekly to participants in both conditions if their behavioral average measuring standardized improvements for dietary and activity goals meets criterion for correct use of the app (for data collection) and attainment of behavioral targets (for diet and activity or for stress and sleep management). Consistent with our standard practice, participants will receive compensation for completing all major assessments (in-person and web-based at baseline and weeks 13, 26, and 39). The maximum total that participants will receive is approximately $200.

#### Active control condition: stress and sleep management

Since stress and sleep disturbances are so pervasive and impactful among rural Appalachian residents, this study arm is salient [39]. Protocols, including the use of the app and all assessments, will be identical between the two treatment arms except for intervention content. In the active control condition, goals pertain to stress and sleep management. As in the original MBC2 trial [12], participants in the control condition will focus on three behavioral goals: relaxation, stress reduction, and sleep. Control participants will be coached to perform three relaxation exercises per day (progressive muscle relaxation, mindfulness meditation, and self-hypnosis), and to achieve end goals of ≥ 7.5 h of sleep per day and a 30% reduction in stress over the 12-week intervention. Participants will use the 1 to 10 Subjective Units of Distress Scale (SUDS) to rate their stress [40]. During assessment periods (baseline, weeks 13, 26, and 39), both intervention and control groups will complete assessments for diet, physical activity, sedentary behavior, sleep, and stress.

Our biostatistician will randomize participants who demonstrate all four risk behaviors into either the diet and physical activity treatment arm (MBC2) or the sleep and stress arm (active control). Randomization will be achieved through a permuted block design using SAS v9.4 PROC PLAN. Sequences are not concealed. Allocation sequence and randomization are undertaken by the project biostatistician, Enrollment takes place by the project manager. Randomization will be stratified by sex, as we expect to recruit more women than men. We will employ the SPIRIT checklist (https://www.spirit-statement.org) to ensure standardization of all clinical trial elements.

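### The protocol declares that the allocation sequence is not concealed, and nothing else in it keeps enrolling staff from learning upcoming assignments, so the comparison is open to selection bias.

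*Protocol article*

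**What the plan says.** All the randomization text is in one paragraph of the protocol article, under the heading Active control condition: stress and sleep management.

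- Method: "Randomization will be achieved through a permuted block design using SAS v9.4 PROC PLAN". No block size is given.
- Stratification: "Randomization will be stratified by sex, as we expect to recruit more women than men".
- Concealment: "Sequences are not concealed". The sentence is unqualified.
- Roles: "Allocation sequence and randomization are undertaken by the project biostatistician, Enrollment takes place by the project manager".
- Standard invoked: "We will employ the SPIRIT checklist".

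Three other places bear on the point. Ethics and dissemination says who takes consent: "Informed consent was obtained by the project manager and staff, all of whom will obtain needed certifications". The Overview of the adapted intervention gives the order of steps: "two-tiered assessment of eligibility, baseline assessment, randomization, 12 weeks of telephone-delivered coaching". Eligibility and screening, written for the pilot and stated to match the main trial, bases entry on reported behaviours: "we limited inclusion to those individuals who reported all of four problematic diet and physical activity behaviors". No section describes a concealment mechanism, and none contradicts the sentence on concealment.

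**The concern.** A condensed article may leave details of concealment to the full protocol. Here, however, the article makes a positive statement that there is none, so the point does not rest on silence.

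Concealment protects the step before assignment. If the person who can hasten, defer or discourage an enrolment may know which arm comes next, the two arms may differ at entry in ways that chance does not govern. A difference in the primary composite could then partly reflect who was placed where. Stratifying by sex does not address this. The Analyses section foresees confounder adjustment for secondary comparisons, but adjustment cannot remove imbalance in something unmeasured, such as motivation.

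Several features of this trial make the exposure more than formal:

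- The role that enrols also takes consent, and staff contact candidates and schedule the steps.
- Entry depends on reported behaviours and on some judgement, for example whether a dietary regimen is incompatible.
- Under the pilot procedure, which the main trial follows with listed exceptions, candidates log a practice period and then a baseline period in the app before assignment. Staff may therefore see who logs diligently.
- The Outcomes section takes the primary outcome from that same app data, so such diligence is plausibly prognostic.

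**Working it through.** **No planned figure to reproduce.** The point rests on a stated rule. The check is therefore a reading of the text, followed by an illustration of scale.

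**Step 1. Does anything in the document supply concealment?**

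| Provision | What it does | Is it concealment? |
|---|---|---|
| Biostatistician generates the list and randomizes | Puts generation and assignment with a role other than the enroller | No. It does not say the list is withheld from others, and the same paragraph says it is not concealed |
| Project manager enrols | Separates enrolment from assignment | No, for the same reason |
| Eligibility and baseline come before randomization | Narrows the time in which an enrolment can be steered | No. A candidate can still be hastened, deferred or discouraged before assignment |
| Permuted blocks | Balances numbers within sex | No. Blocks make later positions partly predictable from earlier ones |

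Nothing in the table prevents enrolling or consenting staff from learning the next assignment.

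**Step 2. Predictability of permuted blocks.** Block size is not given, so a range is shown, assuming 1:1 allocation and knowledge of past assignments only. In a block of 4 the last position is always certain. The third is certain when the first two were alike, which has probability 1/3. The certain share is (1 + 1/3)/4 = 33%.

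| Assumed block size | Assignments that are certain | Best guess correct |
|---|---|---|
| 2 | 50% | 75% |
| 4 | 33% | 71% |
| 6 | 25% | 68% |
| 8 | 20% | 67% |

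These figures describe a list that is itself hidden. Anyone who could actually read an open list would know every assignment. The table matters for the fix: hiding the list is not enough if a fixed block size is known.

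**Step 3. What an imbalance would do to the test.** Inputs: two-sided 5% level, 120 per group (240 in total) and 350 randomized, all from the Analyses section. The allocation ratio is not stated. 1:1 is assumed, giving 350/2 = 175 per arm. Let d be the prognostic difference between arms, in SD units, caused by steering. This is an assumption, not a figure from the document. With no true effect, the test statistic is centred at δ = d × √(n/2), and the rejection rate is approximately

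1 − Φ(1.96 − δ) + Φ(−1.96 − δ).

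- n = 120, d = 0.1: δ = 0.1 × √60 = 0.775. Rate = 0.118 + 0.003 = 0.121 (t-test 0.120).
- n = 175, d = 0.1: δ = 0.1 × √87.5 = 0.935. Rate = 0.153 + 0.002 = 0.155 (t-test 0.154).

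The same formula over a range of assumed imbalances gives:

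| Assumed imbalance d | 120 per arm | 175 per arm |
|---|---|---|
| 0.05 SD | 7% | 8% |
| 0.1 SD | 12% | 15% |
| 0.2 SD | 34% | 46% |

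The 0.2 SD row corresponds to steering that shifts each participant's expected outcome by 0.1 SD up or down according to a fully known next arm (2 × 0.1 = 0.2). If staff could only guess from past assignments, the same shift gives a difference of 2 × 0.1 × (2G − 1), where G is the proportion guessed correctly. For blocks of 2 to 8 this is 0.10 down to 0.07 SD, and an error rate of about 16% down to 10% at 175 per arm.

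**The case against.** The strongest reply is that the text already separates the roles. The biostatistician holds the sequence and assigns, the project manager only enrols, and assignment comes after eligibility and baseline work that takes at least some weeks. On this view little opportunity for steering remains. Much of this stands. The document names nobody outside the biostatistician's role who can see the list, and the order of steps does narrow the opportunity. Neither amounts to concealment, which the paragraph expressly disclaims.

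A second reply is that the sentence is a slip, perhaps meant to say that arms are not blinded after assignment. That is possible, but nothing in the document supports it. If it is so, the sentence is still wrong and needs correcting.

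A third reply is that the error rates rest on assumptions. That is true. Block size, allocation ratio and the amount of steering are all assumed, and the results run from 7% to 46% across the range shown.

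A reader might go further and infer that enrolling staff do foresee the next arm, or that all assignments are known in advance. The document does not support this, because it does not say that the project manager or other staff have access to the list. Nor does it say that relatives or acquaintances enrol together. It opens eligibility to co-residing adults and describes word-of-mouth recruitment, which makes pressure over a particular placement plausible but does not show it.

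**Conclusion.** The concern holds as a stated design weakness. The protocol declares an unconcealed sequence, and its other provisions do not stop enrolling or consenting staff from learning upcoming assignments. The randomized comparison is therefore open to selection bias. The document neither shows that bias has occurred nor fixes how large it could be.

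The 12% and 15% error rates illustrate a 0.1 SD imbalance only, with 1:1 allocation assumed for the larger figure. Stronger assumed steering gives higher rates. The conclusion does not depend on these figures. It rests on the sentence itself and on the absence of any mechanism that offsets it. Because analysis cannot reliably undo the problem afterwards, the sentence should be put right before further participants are randomized.

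**What to change.** Replace the sentence on concealment with wording to this effect:

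*The allocation sequence and block sizes are withheld from all staff who screen, consent, enrol or schedule participants. Block sizes vary at random within each sex stratum. The biostatistician releases each assignment centrally, one at a time, only after eligibility, consent and baseline data have been recorded and locked.*

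The present order of steps already places baseline before randomization. What is new is the withholding, the varying block sizes, the locking and the release one at a time.

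If the sentence was a slip, correct it and state who could access the sequence before assignment.

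The Overview says implementation has begun. If any participants were randomized with an open sequence, report how many and add a sensitivity analysis by period (open versus concealed).

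The cost is a few hours of set-up and a protocol modification to the IRB, with no extra participants or staff. Allocations already made openly cannot be repaired. The sensitivity analysis would only show whether the result differs between periods.
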